**FIGURE 1 F1:**
[figure not shown]
Condition 1: Enhanced *data collection*.

**FIGURE 2 F2:**
[figure not shown]
Condition 2: Enhanced *data control*.

**FIGURE 3 F3:**
[figure not shown]
Condition 3: Enhanced *third party sharing*.

Designing these hypothetical premium versions as realistic as possible, we will rely on Facebook’s Data Policy to extract three central privacy aspects, namely data collection, data control, and third party sharing (Facebook Inc., 2016). We will adapt relevant parts of the policy accordingly to match the increased privacy functionalities of our premium versions. The conventional, free version of Facebook used for side-by-side comparisons consists of shortened and simplified, but otherwise unaltered, parts of Facebook’s original Data Policy. The premium versions are written in such a fashion to correspond to the original policy as much as possible, while enhancing specific privacy aspects. To facilitate readability, this information is presented in form of concise and comprehensive bullet points.

### Willingness-to-Pay Measure

Quantifying Internet users’ valuation of the different privacy aspects, the van Westendorp’s (1976) Price Sensitivity Meter model (PSM) will be employed as a willingness-to-pay measure. The PSM is a descriptive statistical procedure labeled the “psychological price” modeling (Lipovetsky et al., 2011). Rather than asking a single price indicator, the PSM allows capturing economic valuation in psychological terms. Furthermore, it ensures comparability of the results with the study by Schreiner et al. (2013). The PSM consists of four questions that ask participants to balance the value of certain products or services against the price. Precisely, participants will answer the following questions about the four premium versions (as compared to the free version) presented:

(1)At what price does this product become *too cheap*, that is, so cheap that you would question its quality and not buy it?(2)At what price does this product start to seem *cheap* to you, that is, when does it start to seem like a bargain?(3)At what price does this product start to seem *expensive* to you?(4)At what price does this product become *too expensive*, that you would not consider buying it?

The questions will be presented simultaneously and in the above order below the two versions of Facebook (i.e., conventional, free-of-charge versus hypothetical, privacy-enhanced version of Facebook). Participants will be asked to indicate a monthly price they are willing to pay for the privacy enhancement of each premium version. Combining the answers from the four PSM questions will allow identifying the upper and the lower price limit that participants are willing to pay for privacy. Based on this, the optimal price can be calculated as described in more detail in Section Proposed Analysis.

After answering the four PSM questions, a single-item willingness-to-pay measure will be employed to additionally assess the overall willingness-to-pay for the different privacy aspects (“*Overall, how much would be willing to pay for this premium version of Facebook?”)*. This overall valuation measure will be used to validate the results of the PSM and to conduct the multiple comparisons between the three privacy enhancements, which will allow drawing conclusions about which privacy aspects are valued the most.

### Theoretical Model

To unravel the psychological mechanisms underlying privacy valuations on social networking services, a theoretical model will be tested. The present model is developed based on previously suggested models by Wilson and Valacich (2012) and Malhotra et al. (2004). The theoretical model presented here outlines the expected relationships between the psychological variables in predicting Internet users’ privacy valuations on social networking services (see **Figure 4**). The modeled psychological variables are selected based on previous research demonstrating their relevance in the context of information privacy. Where necessary, the psychological measures are adapted to suit the context of Facebook.

**FIGURE 4 F4:**
[figure not shown]
Theoretical model underlying privacy valuations.

The present model proposes that perceived risk on Facebook mediates the relationship between privacy concerns (see also Malhotra et al., 2004) in predicting valuation of privacy, and that this relationship is further moderated by trust in Facebook and its Data Policies (adapted from Milne and Culnan, 2004) as well as by the level of Facebook use (adapted from Jenkins-Guarnieri et al., 2013). More specifically, we propose that high levels of privacy concerns predict high willingness-to-pay for privacy, mediated through increased privacy-related risk perception on Facebook. Additionally, the valuation of privacy is expected to depend on Facebook members’ current Facebook use or non-members’ perceived usefulness of Facebook, respectively (adapted from Rauniar et al., 2014). Among frequent Facebook users, those with greater privacy concerns are expected to express greater willingness-to-pay for privacy on Facebook than those with lower privacy concerns. Among non-members of Facebook, those with strong privacy concerns and perceptions of Facebook’s usefulness are expected to express higher willingness-to-pay for privacy than those non-members who do not perceive Facebook as useful. The rationale behind this is that privacy-concerned people who perceive Facebook as useful but are not member of the network, may abstain due to their privacy concerns, rather than due to lacking benefits from Facebook membership, and may thus be more likely to pay for privacy on Facebook. In addition to these psychological characteristics, socio-demographic information and the psychological characteristics social norms and comparative optimism will also be assessed, as these may have additional explanatory power beyond the primary variables included in the model. The psychological characteristics and socio-demographic information that are expected to explain participants’ privacy valuations are explained in more detail in the next section (see Section Psychological Characteristics).

### Psychological Characteristics

#### Privacy Concerns

The IUIPC scale developed by Malhotra et al. (2004) is a widely used measure of privacy concerns consisting of 10 items. The items (e.g., *“It usually bothers me when online companies ask me for personal information”*) assess the three privacy dimensions data collection, data control, and awareness of the company’s data practices on a 7-point Likert scale from one (strongly disagree) to seven (strongly agree). All three subscales have a composite reliability score of above 0.70 and have been validated in predicting behavioral intentions and Internet users’ reactions to online privacy threats (Malhotra et al., 2004). The relationship between privacy concerns and willingness-to-pay for privacy on social networking services will be examined. It is hypothesized that high levels of privacy concerns will predict greater willingness-to-pay for privacy directly through perceived risks on Facebook as well as through moderation of further psychological characteristics.

#### Perceived Risk on Facebook

Along with the IUIPC, Malhotra et al. (2004) used and adapted the risk perception scale validated by Jarvenpaa et al. (1999). As suggested in Malhotra et al. (2004), we adapted the six risk perception items to make them specific to the context of Facebook (e.g., *“The risk that personal information submitted to Facebook could be misused is immense”*). The scale has a reliability score of Cronbach’s α = 0.70 and uses a 7-point Likert scale ranging from one (strongly disagree) to seven (strongly agree). We hypothesize perceived risk on Facebook to be the main mediator of the effect of privacy concerns on willingness-to-pay. For participants with high privacy concerns but low risk perceptions on Facebook, however, valuation of privacy is expected to be low.

#### Perceived Internet Privacy Risk and Personal Internet Interest

Two scales will be used that were developed and validated by Dinev and Hart (2006a) and measure general Internet privacy risk and interest. Perceived Internet privacy risk consists of four items (e.g., *“I am concerned that the information I submit on the Internet could be misused”*), while personal Internet interest consists of three items (e.g., *“The greater my interest to obtain a certain information or service from the Internet, the more I tend to suppress my privacy concern”*). The items are assessed on a 5-point Likert scale ranging from one (very low risks/strongly disagree) to five (very high risk/strongly agree). For both scales, Cronbach’s alpha indicates reliability above 0.66, which is the recommended cut-off score (Nunnally, 1978). Dinev and Hart (2006a) find that higher privacy risk perceptions are related to higher levels of privacy concerns and lower willingness to transact personal information on the Internet, and that higher Internet interest is related to higher willingness to transact personal information on the Internet. While perceived risk on Facebook (see Section Perceived Risk on Facebook) is included as the main mediator in the model, the more general perceived Internet privacy risk measure will be tested as potential moderator for non-members of Facebook.

#### Trust in Facebook

Trust has been described as important foundation for all economic transactions (Ben-Ner and Halldorsson, 2010) and previous research demonstrated that customers’ trust in companies and the Internet are important predictors of online disclosure and sharing behaviors (Metzger, 2004). Trust in the social networking service Facebook will be assessed via the trust in privacy notices subscale by Milne and Culnan (2004), defining trust as consumers’ willingness to accept a level of risk in the face of incomplete information and as their belief that businesses will adhere to the privacy practices they declare (see Gefen et al., 2003 for a review on the trust literature). The relationship between trust in privacy notices with perceived risk and privacy concerns has been validated in Milne and Culnan (2004). In the present study, this relates to the belief that changes in Facebook’s Data Policy can generally be trusted and the scale will be adapted to the context of Facebook. The scale consists of five items (e.g., *“I believe that the Facebook privacy statements are truthful”*), which are assessed on a 5-point Likert scale ranging from one (strongly disagree) to five (strongly agree). The scale’s Cronbach’s alpha is 0.82. Trust is hypothesized to moderate the relationship between privacy concerns and willingness-to-pay for privacy. Precisely, to invoke willingness-to-pay for privacy, participants need to generally trust Facebook and trust in Facebook’s adherence to the offered privacy enhancements.

#### Facebook Use

Facebook use will be measured only among participants who, at the time of participation in this study, are members of Facebook. Facebook use will be assessed using the social media use integration scale by Jenkins-Guarnieri et al. (2013). The validated scale consists of 10 items (e.g., *“I feel disconnected from friends when I have not logged into Facebook”*), which are assessed on a 6-point Likert scale ranging from one (strongly disagree) to six (strongly agree). The scale has a Cronbach’s alpha reliability of 0.91 and assesses social integration in and emotional connectedness to Facebook. It is hypothesized that frequent Facebook use will moderate the effect of privacy concerns through risk perceptions on participants’ willingness-to-pay. Precisely, frequent Facebook users with strong privacy concerns are assumed to indicate greater willingness-to-pay.

#### Perceived Usefulness of Facebook

Perceived usefulness of Facebook will be assessed only in participants who, at the time of participation in this study, are non-members of Facebook. The perceived usefulness scale from the revised social media technology acceptance model (TAM) by Rauniar et al. (2014) will be administered and adapted to the context of Facebook. The scale has been validated by Rauniar and colleagues and consists of five items (e.g., *“Using Facebook makes it easier to stay informed with my friends and family”*), which are assessed on a 5-point Likert scale ranging from one (strongly disagree) to five (strongly agree). The scale has a composite reliability score of above 0.70. We hypothesize that perceived usefulness of Facebook will moderate the relationship between privacy concerns and willingness-to-pay for non-members of Facebook. Precisely, we expect that when non-members of Facebook with high privacy concerns and risk perceptions still consider the usefulness of Facebook to be high, they could be willing to use a version of Facebook that protects their data and therefore indicate a higher willingness-to-pay.

#### Socio-Demographic Information

Previous research showed that socio-demographic factors, such as age and gender, influence Internet users’ valuation of personal data and privacy (e.g., Krasnova et al., 2009). Therefore, socio-demographic information will be assessed, including gender, age, level of education, employment status, type of work, socioeconomic status, country of residence, and nationality. Socioeconomic status is predicted to have an influence on willingness-to-pay, as economic status (e.g., income) impacts people’s overall readiness to pay a certain financial amount for the usage of a service or a product (Onwujekwe et al., 2009). We assume that socio-demographic information will influence the relationship between privacy concerns and willingness-to-pay for privacy on social networking services and control for these influences in our model.

#### Social Norms

Social norms are a strong predictor of human offline behaviors (Cialdini and Trost, 1998) and have been shown to be a significant antecedent of adopting online behaviors too (Chiasson and Lovato, 2001; Spottswood and Hancock, 2017). We will employ the questionnaire developed by Charng et al. (1988) to assess perceptions of social online norms and adapt the questionnaire to the context of Facebook. The questionnaire was validated for online use and has a reliability of Cronbach’s alpha of 0.86 (Choi and Chung, 2013). The five items (e.g., *“Many of the people that I know expect me to continuously use Facebook”*) are assessed on a 7-point Likert scale ranging from one (strongly disagree) to seven (strongly agree). We hypothesize that perceived social norms positively correlate with perceived usefulness of Facebook in non-members and with Facebook use in current Facebook users. Hence, social norms could further moderate the impact of privacy concerns on willingness-to-pay. If confirmed in the analysis, this variable may be included in the theoretical model.

#### Comparative Optimism

Participants’ comparative optimism in the online context will be assessed using the approach by Baek et al. (2014). This approach relies on the indirect method (Harris et al., 2000) to assess participants’ likelihood estimation of experiencing a certain event as compared to others experiencing the same event. In two separate items, participants make judgments about their perceived personal and target group risk (i.e., *“How likely are you [target group] to fall victim to improper use of online information?”*). Both items will be assessed on a 5-point Likert scale ranging from one (least likely) to five (most likely). It is expected that participants who underestimate their own risk to fall victim to improper use of online information, as compared to others, have lower privacy concerns and risk perceptions, which may result in lower willingness-to-pay for privacy. Similar to social norms, we will test the relevance of this variable for the model.

## Stepwise Procedures

The present experiment will be administered online using the web-based survey tool Qualtrics that allows designing, running, and collecting data through online experiments and surveys. The stepwise procedures of the experiment are as follows: After informed consent is given, participants will first answer a baseline measure that assesses if participants would be willing to pay for the current, free-of-charge version of Facebook. Afterward, participants will be presented a short vignette describing a scenario in which Facebook may consider developing premium versions of their service that would offer enhanced privacy for users in return for a monthly fee. In the first part of the online experiment, four hypothetical, privacy-enhanced premium versions of Facebook are presented consecutively and participants indicate their willingness-to-pay for each of the premium versions using the four questions of the PSM and the additional overall willingness-to-pay item (see Section Willingness-to-Pay Measure). Each privacy-enhanced version of Facebook is contrasted with the conventional, free-of-charge version of Facebook to facilitate comparability and increase participants’ understanding of the enhancements of the premium versions. To control for order effects, the three privacy-enhanced premium versions of Facebook (i.e., data collection, data control, and third party sharing) will be presented in randomized order. The fourth full-design premium version, which combines all three privacy enhancements in one version, will be presented last.

The second part of the study will assess several psychological characteristics (see Section Psychological Characteristics) to test the proposed theoretical model (see Section Theoretical Model) that specifies the psychological mechanisms underlying Internet users’ privacy valuations. The items of each scale will be presented in randomized order. Short control questions will be included in the online survey to ensure participants understand the privacy enhancements in the premium versions and to assess for how useful, credible, and technologically feasible these are rated. Two more general items will control whether participants answer the online study truthfully (e.g., *“In general, I answered all of the questions seriously”*). Lastly, socio-demographic information will be assessed. Once the survey is completed, participants will be thanked and further debriefed about the topic and purpose of the present study and those interested can read more about privacy and how to protect their online data. Those participants wishing to enter the prize draw will be invited to follow a link to a separate survey where they can enter their email addresses. This way participants’ anonymity will be preserved and linking survey responses to identifiable information will be avoided.

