**FIGURE 7 F7:**
[figure not shown]
Price sensitivity for the acceptable price perception interval.

Ordinal logistic regression models will be applied to test for statistical differences between participants’ willingness-to-pay for the different privacy aspects captured in the hypothetical premium versions of Facebook. Furthermore, the regression models can be extended to multiple predictors (e.g., privacy concerns and socio-demographic characteristics), since we hypothesize that psychological characteristics influence participants’ propensity to pay for the privacy enhancements. Together with the range of acceptable prices, the proxies will be used to test for intra-individual and inter-individual differences between willingness-to-pay for the four privacy-enhanced premium versions of Facebook. In addition, repeated-measure ANOVAs will be calculated for participants’ willingness-to-pay for the four different premium versions of Facebook, using the participant answers on the overall valuation measure (i.e., *“Overall, how much would be willing to pay for this premium version of Facebook?”*) as dependent variable. Where applicable, *post hoc* tests will be employed to determine the specific group differences. Data analysis will be conducted in R studio (R Core Team, 2017) and the conventional significance level of α = 0.05 will apply to all analyses.

With respect to the theoretical model (see **Figure 4**, Section Theoretical Model), we follow previous approaches (Malhotra et al., 2004; Schreiner and Hess, 2015) and assume linear relationships between the indicated psychological variables (see Section Psychological Characteristics), which will be statistically tested using structural equation modeling to identify the path coefficients. As outcome variable in the tested model, participants’ overall willingness-to-pay for the hypothetical, full-design premium version of Facebook will be used.

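### Randomising the order of the three single-aspect versions balances average position effects but not carry-over, and the described analysis makes no use of the known order (minor)

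*Protocol article*

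**What the plan says.** Stepwise Procedures describes a within-person design in which "four hypothetical, privacy-enhanced premium versions of Facebook are presented consecutively". Each version takes five price answers: the four Price Sensitivity Meter questions and one overall willingness-to-pay item. The three single-aspect versions come in random order with an explicit aim, "To control for order effects, the three privacy-enhanced premium versions of Facebook" "will be presented in randomized order". The combined version is outside the randomisation: "The fourth full-design premium version, which combines all three privacy enhancements in one version, will be presented last".

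Proposed Analysis gives two comparisons of versions. For the price-meter answers, "Ordinal logistic regression models will be applied to test for statistical differences between participants’ willingness-to-pay for the different privacy aspects", and it adds that "the regression models can be extended to multiple predictors (e.g., privacy concerns and socio-demographic characteristics"). For the overall item, "repeated-measure ANOVAs will be calculated for participants’ willingness-to-pay for the four different premium versions of Facebook", with post hoc tests where applicable. The Willingness-to-Pay Measure section assigns the overall item to the comparisons among the three aspects. Neither analysis names position, order or preceding version. The limitations listed under Anticipated Results do not mention carry-over.

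**The concern.** Order effects are of two kinds. A position effect is a general shift from being asked first, second or third, and random order balances it across aspects. Carry-over is the influence of one version's price on the price given to the next, for example by anchoring. Random order spreads carry-over over the aspects but does not remove it.

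The protocol's claim of control does not distinguish the two, and the order created by the randomisation is not used in the analysis as described. The first objective is whether some aspects are valued more than others, and the size of the price gaps is itself a result. If carry-over occurs, those gaps could be misstated and the described analysis would give no sign of it. Separately, leaving position out gives up a little precision.

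**Working it through.** **Inputs.** From the protocol: three single-aspect versions in random order (six possible orders), a recruitment target of 350 and a minimum of 256. The protocol gives no figure for position effects, carry-over, SDs or within-person correlation, so there is no figure of its own to reproduce on this point. Assumed for illustration, in price units: between-person SD 0.8, within-person SD 0.6, true contrast between two aspects 0.20, position shifts of 0.2 or 0.3 per step, assimilation weight L from 0 to 0.6.

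**1. Position effects only: bias.** In simulation with shifts of 0/+0.2/+0.4 or 0/-0.3/-0.6, the ANOVA without a position term gave mean contrasts of 0.199 to 0.202 (true 0.200). Type I error under no difference was 0.044 to 0.052. Randomisation does its job here.

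**2. Position effects only: precision.** The per-person variance of a contrast is 2 × 0.6² = 0.72 plus the variance of the position difference between the two versions. That difference is one step with probability 4/6 and two steps with probability 2/6.
- Shift 0.2: (4/6)(0.04) + (2/6)(0.16) = 0.08. SE = √(0.80/350) = 0.048.
- Shift 0.3: (4/6)(0.09) + (2/6)(0.36) = 0.18. SE = √(0.90/350) = 0.051.
- Position in the model: SE = √(0.72/350) = 0.045.

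The gain from adding position is a confidence interval that would otherwise be about 5% to 12% wider (√(0.80/0.72) = 1.05; √(0.90/0.72) = 1.12).

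**3. Carry-over by assimilation.** Let aspects A, B and C have true values a, b and c. Let the first price equal the true value, and each later price equal (1-L) times the person's own value plus L times the first price. Over the six orders:
- Mean price of A = a(1 - 2L/3) + (L/3)(b + c).
- Contrast A - B = (a-b)(1 - 2L/3) - (a-b)(L/3) = (a-b)(1-L).
- By position: (a-b) at position 1, and (a-b)(1 - 1.5L) at positions 2 and 3. The average is [1 + 2(1 - 1.5L)]/3 = 1-L, which agrees.

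Anchoring on the preceding price instead of the first gives the same result. A true gap of 1.00 is estimated as 0.80, 0.70 or 0.50 for L = 0.2, 0.3 or 0.5.

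**4. Would a position term repair this?** No. With a true contrast of 0.200 and L = 0.2, 0.4 or 0.6, the simulated contrast was about 0.160, 0.120 or 0.080 with or without a position main effect. The trace of carry-over is in the version-by-position pattern, and only the first-shown comparison is untouched by it.

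**5. Precision of the first-shown comparison.** It is between persons, with total SD √(0.8² + 0.6²) = 1.0.
- At 350: 350/3 ≈ 117 per version, SE = √(2/116.7) = 0.13.
- At 256: 256/3 ≈ 85 per version, SE = √(2/85.3) = 0.15.
- Within persons: 0.6√(2/350) = 0.045 and 0.6√(2/256) = 0.053 (simulated value at 350: about 0.046).

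The difference between the first-shown and within-person contrasts has SE about √(0.131² - 0.045²) = 0.12 at 350, against an expected discrepancy of L times the true gap. With L = 0.3 that is 0.15 for a gap of 0.5 and 0.30 for a gap of 1.0. Only large carry-over would be visible.

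**The case against.** The strongest reply is that nothing in the protocol is false. Randomised order does control position effects, and the precision lost by ignoring position is small. An interaction check or a first-shown sensitivity analysis is commonly left to a statistical analysis plan, and that plan is not shown. The list of possible extra predictors is open, and nothing rules out using the order. Carry-over is nowhere documented, and contrast effects could act in the opposite direction to anchoring. Most of this stands, and it is why the point is minor. What remains is that the protocol claims control of order effects without limiting the claim, and describes an analysis that leaves the known order unused.

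Three stronger readings are tempting and are not supported.
- A reader might infer that omitting position causes the gaps to shrink. It does not: any shrinkage comes from pricing several versions in sequence, and a position main effect leaves it unchanged.
- A reader might infer that a finding of equal valuation could be produced by anchoring. In the simulation at 350 the error shrank along with the contrast, and ANOVA power was 0.95 to 0.99 with anchoring against about 0.98 without it.
- A reader might infer that the ranking of aspects is at risk. Uniform assimilation with L below 1 multiplies every contrast by the same factor and keeps the ranking. A changed ranking would need anchoring that differs by aspect, for which the documents give no basis.

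**Conclusion.** The point holds as a minor one. Randomised order keeps the aspect contrasts unbiased under average position effects, but it does not remove carry-over, and the described ANOVA does not use the order. The cost that arises whenever position matters is a modest loss of precision: an SE of 0.048 to 0.051 instead of 0.045 at 350, under the assumed SD and shifts. The conditional cost is a misstated gap between aspects, smaller by (1-L) under assimilation or larger under contrast effects, which the described analysis would not reveal. L, the SDs, the position shifts and the assimilation model are all assumptions. The documents support neither a claim that carry-over is present nor a claim that the planned comparison is invalid.

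**What to change.** - In the three-version comparison of the overall item, add presentation position (1 to 3) as a within-person factor alongside version. Each person sees a version in only one position, so a mixed model with a participant effect is the convenient form. Keep the combined version out of this model: it is always fourth, so its version and position effects cannot be separated.
- Pre-specify, as supporting analyses, the version-by-position estimates and the between-participant comparison of the first version shown. Report both descriptively with confidence intervals. Do not use them as a pre-test that changes the primary result.
- Reword the statement in Stepwise Procedures so that randomised order is said to balance average position effects, and add possible carry-over to the limitations.

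The cost is a few sentences of analysis text and keeping the presentation order in the data set. The downside is that the first-shown contrast is nearly three times less precise than the within-person one (SE about 0.13 against 0.046 under the assumed SDs). It can therefore expose only large carry-over, and a wide interval there should not be read as showing that none exists.
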